### Sample size and power analysis

**Table 3 Tab3:** Number of planned participants by site and intervention type

	Site 1 (SEED Method)	Site 2 (SEED Method)	Site 3 (Delphi method)
**Intervention**	24 (3 groups of 8)	24 (3 groups of 8)	24 (1 group, with number of specific stakeholder groups TBD)
**Control**	24	24	24

The power analysis is calculated based on the sample sizes of the intervention and control group participants only. A target number of 48 participants per community will be recruited and randomized to the intervention or control condition (24 per condition) (Table 3). Minimal detectable differences between the variables of primary interest were estimated with this sample size, setting the alpha error at 0.05 and the beta error at 0.20, adjusting for the estimated ICC and the usual population variances based on cited research (Table 4). Based on these analyses, the anticipated sample size will have an 80% probability of detecting treatment differences in the primary outcomes if the true differences are in the range of the minimum detectable differences. These scores were calculated based on the standard deviations reported by Kasmel and Tanggaard [38].

**Table 4 Tab4:** Minimum detectable differences (MDD) in primary outcome variables

Minimum Detectable Difference (MDD) and Percent Minimum Detectible Difference (%MDD)			
Estimated *n* = 144	$$\:\underset{\_}{x}$$ ^*^	SD^*^	MDD (%MDD)
Mobilization Scale (Total)	1.87	0.37	0.12 (6.5)
Participation Subscale	1.70	0.56	0.18 (10.9)
Motivation Subscale	1.83	0.56	0.18 (10.1)

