### Recruitment

Recruitment will occur through a combination of outreach strategies, including personal contacts, flyers and messages sent to partner organizations to be shared with potential participants, social media postings or advertisements, and advertisements in local media. The outreach materials will provide contact information for the study coordinator. The study coordinator will review eligibility criteria with potential participants and confirm eligibility for a specific stakeholder group within the relevant site. Once deemed eligible, the research coordinator will obtain informed consent. The target is 48 participants per county (144 total) divided as follows: 24 in the intervention group (For the SEED Method they are further divided into three stakeholder Topic groups) and 24 in the control group (composed of an equal number of stakeholders from each group). These are our target numbers, but flexibility will be allowed which may result in some stakeholder groups being larger or smaller than the target based on the community research teams’ ability to recruit.

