### Evaluation activities

All research participants and community research team members will be included in the evaluation. Intervention and control group participants will be given an online pretest near the start of participation and an online posttest after activities are completed, as well as a follow-up survey approximately one year after the posttest (Table 2). Community research team members at the three sites will receive the same pre-, post-, and follow-up surveys. Focus group participants will receive a brief pre- and posttest survey only. For a subset of analyses, we will compare responses by participant type (intervention and control group participants, community research team members, and focus group participants). The evaluation surveys are distinct from the surveys taken by the Delphi method and control group participants. The former are designed to assess changes in key outcome measures (i.e., mobilization, motivation, and participation) to assess the impact of participatory research approaches on civic engagement, while the latter ask participants to propose and prioritize strategies to address opioid misuse in their communities.

**Table 2 Tab2:** Evaluation data collection activities for RCT participants

	Pretest	Posttest	Follow-up
**Topic Group/** **Delphi Group – Intervention**	Demographic Survey Mobilization scale Community engagement survey Group dynamics (selected) Group readiness	Mobilization scale Community engagement survey Interview Group dynamics Process questions	Mobilization scale Community engagement survey Open ended responses
**Control**	Demographic Survey Mobilization scale Group readiness (selected)	Mobilization scale Process questions	Mobilization scale

A second outcome measure is strategy development (the number, type, and diversity of strategies created). To compare strategies across groups, members of the research team will code the strategies to indicate the focus, or domain, of each question. We will use the codes to calculate the number of domains addressed by each group and the number of domains (if any) that were unique to that group.

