### Data analysis

For the survey data, descriptive univariate analyses will be conducted on all study variables. The data will be checked for outliers, violations of normality and missing data. Predictors of drop-out and nonresponse will be explored to better understand any discernible systematic processes in play, taking advantage of the data collected until the last time point and demographic variables. If the missing data are found to be random and ignorable, multiple imputations will be used to address missing data [42]; otherwise, an intent-to-treat approach that makes full use of available data in determining intervention effects will be used for all analyses.

Scale scores will be calculated for all outcomes. The first step will be to calculate the intraclass correlation coefficient (ICC) to determine what percentage of the variance in the dependent variable is attributed to being from the same community. If the ICC at the community level is negligible, the community will not be used in the nested structure, and robust standard errors will be estimated to correct for the nested data structure. For primary and secondary outcomes, a two-level clustered longitudinal model with growth trajectories (change from Year 1 to Years 2 and 3) will be assessed at level 1 for each participant; variation in growth parameters among participants depending on the treatment status nested within location will be captured in the level 2 model. STATA will be used to estimate these two-level models. Covariates at different levels will be included at the two levels as predictors to isolate the effects on treatment outcomes. The two-level longitudinal model in STATA can be utilized for continuous as well as categorical and binary outcomes with minor changes in the interpretation of coefficients.

Data collected during the focus groups is for the purpose of including additional perspectives to the community research team members and Topic group members. Analysis of the data will focus on identifying themes from the information shared in the focus groups and summarizing them for discussion.

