## Discussion

With the increasing popularity of community engaged research, there is an urgent need for data on the effectiveness of different engagement methods to help researchers and community partners make decisions about which methods are best suited to their needs. This research protocol describes a study comparing the effectiveness of two community engagement methods, the SEED Method and the Delphi method, and a control intervention. Participants in three rural counties will create local strategies for addressing opioid misuse and prioritize those strategies for use in community action planning. Community members participating in the study represent a range of relevant stakeholders. We will assess changes in the self-rated civic engagement of participants and compare the number and types of strategies created and prioritized using the three methods evaluated. This protocol describes a group randomized controlled trial to evaluate the effectiveness of these methods on increasing the civic engagement of participants and on the number, quality, and type of strategies created. Given the design of the study, we will be able to compare the SEED Method to the Delphi Method and compare both of these methods to the control group. We will also be able to explore how effects differed depending on participant role (community research team member, intervention/control group participant, and focus group participant).

The strengths of this protocol include replicating the implementation of the SEED Method, which was previously used in a rural Virginia county and a large midwestern city, to develop community strategies for reducing opioid misuse. Furthermore, we will use a rigorous randomized design with data collected at three time points. While the protocol was developed collaboratively with the previous developers of the SEED Method, an independent evaluation team will collect and analyze the data. Limitations could include the small sample size and the use of a relatively new outcome measure (the Mobilization Scale). Further limitations could result from the ability to recruit and retain the target number of participants in the rural communities. While we have specified recruitment targets and project activities, this is community-led research, and some decision-making will take place during implementation by community teams, which is considered a normal part of the process.

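### Table 4 and the 80% power statement use all 144 randomised participants as the number analysed, with no allowance for missing outcomes

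*Protocol article*

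**What the plan says.** Under Sample size and power analysis, the protocol states: "A target number of 48 participants per community will be recruited and randomized to the intervention or control condition (24 per condition". It continues: "Minimal detectable differences between the variables of primary interest were estimated with this sample size". On the error rates, the same sentence adds "setting the alpha error at 0.05 and the beta error at 0.20". Table 4 is headed "Estimated *n* = 144" and gives an MDD of 0.12 (6.5%) for the Mobilization total, 0.18 (10.9%) for Participation and 0.18 (10.1%) for Motivation. An 80% chance of detecting differences of that size is then claimed for the anticipated sample.

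The Recruitment section gives the same number as the enrolment goal: "The target is 48 participants per county (144 total) divided as follows: 24 in the intervention group". It allows groups to end up larger or smaller than that.

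The Abstract defines the primary outcome as change in the total score. Evaluation activities schedules a pretest, a posttest and "a follow-up survey approximately one year after the posttest". Data analysis models change from Year 1 to Years 2 and 3 and says "Predictors of drop-out and nonresponse will be explored", with imputation or use of all available data to follow. The Discussion adds: "Further limitations could result from the ability to recruit and retain the target number of participants in the rural communities".

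**The concern.** The number to be randomised serves as the number analysed. A participant lost before the posttest contributes no observed change, and one lost before the follow-up contributes nothing observed at that survey. Any such loss raises the detectable difference above the value in Table 4.

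What is at stake is how the result is read. A null finding would be presented as coming from a trial with 80% power at the printed differences, although that power was calculated for complete data.

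**Working it through.** **Inputs.** From Table 4: total score mean 1.87, SD 0.37, MDD 0.12 (6.5%); Participation mean 1.70, SD 0.56, MDD 0.18 (10.9%); Motivation mean 1.83, SD 0.56, MDD 0.18 (10.1%). From the text: alpha 0.05, power 0.80, allocation 72 to 72 (24 per arm in each of three counties). Assumed: two-sided alpha (sidedness is not stated) and equal loss in both arms of 10%, 20% or 30% (no rate is stated).

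**Step 1: reproduce Table 4.** With z-values 1.960 + 0.842 = 2.80, the three printed percentages are recovered by MDD = 2.80 × SD / √72:

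- Total: 2.80 × 0.37 / √72 = 0.1222, and 0.1222 / 1.87 = 6.5%
- Participation: 2.80 × 0.56 / √72 = 0.1849, and 0.1849 / 1.70 = 10.9%
- Motivation: 0.1849 / 1.83 = 10.1%

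This contains no deduction for loss. It is not, however, the plain two-sample formula for 72 against 72, which is taken up in Step 4.

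**Step 2: effect of loss on the MDD.** The MDD varies as 1/√n, so a loss fraction d multiplies it by 1/√(1 − d), whichever base formula was used.

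| Loss assumed | Number with outcome | Multiplier | Total-score MDD, from 0.1222 | % of mean 1.87 |
|---|---|---|---|---|
| 0% | 144 | 1.000 | 0.122 | 6.5 |
| 10% | 129.6 | 1.054 | 0.129 | 6.9 |
| 20% | 115.2 | 1.118 | 0.137 | 7.3 |
| 30% | 100.8 | 1.195 | 0.146 | 7.8 |

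The subscale value of 0.185 becomes 0.195, 0.207 and 0.221.

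**Step 3: power at the full-sample MDD.** Power = Φ(2.80 × √(1 − d) − 1.96):

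- 10%: Φ(2.658 − 1.960) = Φ(0.698) = 76%
- 20%: Φ(2.506 − 1.960) = Φ(0.546) = 71%
- 30%: Φ(2.344 − 1.960) = Φ(0.384) = 65%

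**Step 4: the separate discrepancy in the base formula.** For two arms of 72, MDD = 2.80 × 0.37 × √(2/72) = 0.173 (9.2%), not 0.12. The ratio is √2. The printed value fits 144 per arm, a one-sample test of 72, or 72 against 72 with an unstated pre-post correlation of about 0.75 (change score) or 0.7 (baseline-adjusted). None of these three readings includes an inflation for the ICC, although the text says one was made.

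From the plain two-sample value of 0.173, losses of 10%, 20% and 30% give 0.182, 0.193 and 0.207. With whole arms of 64 and 57 and the t distribution, the values are 0.185 and 0.196.

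Of the move from 0.122 to 0.193 at 20% loss (a factor of 1.58), the factor 1.41 is the base formula and only 1.12 is attrition.

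**The case against.** The case for leaving the text alone has four parts.

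- **The protocol forecasts no loss.** A reader might infer that it expects drop-out and so contradicts its own power statement. The text does not go that far. Data analysis says how drop-out will be examined and handled, and the Discussion says only that limitations could arise. There is no forecast and no rate, so this is an unstated assumption of complete data, not a contradiction.
- **No time point is attached to Table 4.** A reader might infer that 80% power is claimed at the one-year follow-up. The power section does not say so. The point stands regardless, because posttest nonresponse matters too.
- **The planned analysis uses partial data.** Someone with a pretest and posttest but no follow-up still contributes, and imputation draws on what was observed. This is right, and it makes completer-only figures close to a worst case for a given loss rate. It does not bring power back to that of complete data.
- **The article condenses a fuller protocol and already hedges.** It calls the sample size estimated and anticipated, and it lists small sample size and retention as limitations. An allowance might be set out elsewhere. But the article prints a specific number, specific MDDs and an 80% claim, and these rest on the full 144.

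A reader might also take the gap between 0.12 and about 0.19 or 0.20 as the price of attrition. It is not. Most of that gap exists with no loss at all (Step 4).

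**Conclusion.** The point holds in a limited form. The MDDs and the 80% power apply only if all 144 randomised participants supply outcome data, and the protocol makes no allowance for fewer. At assumed equal losses of 10%, 20% and 30%, the MDD is understated by about 5%, 12% and 20%, and power at the full-sample MDD is lower by about 4, 9 and 15 percentage points.

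These sizes rest on assumed rates, two-sided alpha and equal loss by arm. At each rate they are upper bounds, since the longitudinal model and imputation recover part of the information. The proportional effect on the MDD does not depend on which formula lies behind Table 4.

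The √2 discrepancy in Table 4 is a separate and larger matter, and it should not be attributed to attrition.

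**What to change.** 1. Document or correct the formula behind Table 4 first: the number per arm, any pre-post correlation, the ICC value and the sidedness of the test.
2. Keep 144 as the randomisation target. State an assumed loss and the time point (posttest, follow-up or both), and recompute the MDDs on the number expected to have outcome data.
3. Word the 80% statement as applying to that number.

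If the present scale is justified by a documented correlation, the total-score MDD becomes about 0.129 at 10% loss and 0.137 at 20%. If a plain two-sample comparison is meant, the values are about 0.18 and 0.19, and the text should say that most of the change from 0.12 comes from the base formula.

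The cost is a recalculated table and a sentence or two. No extra enrolment is needed. Keeping 144 analysed would instead require randomising 144/0.9 = 160, 144/0.8 = 180 or 144/0.7 = 206 participants, which is not proposed here.

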### Implementation

In each county, a local community research team will lead recruitment and activities. The composition of each community research team is planned as follows: one local Cooperative Extension agent, one project coordinator, and four additional community stakeholders.

In SEED Method counties, the community research teams will use the *SEED Stakeholder Identification Matrices* to identify three groups of stakeholders to engage in the process. The stakeholders are divided into separate groups primarily to emphasize their different perspectives and lived experiences, as well as to maximize affinity within the groups. The three Topic groups will attend seven meetings facilitated by their local community research teams. During these seven meetings, they will learn about the SEED Method process; review and discuss data about opioid use, opioid misuse, local statistics, and services; review focus group data from other stakeholders in their community; discuss relevant themes; engage in participatory conceptual modeling to explore potential causal factors and their interrelationships; participate in facilitated strategy development and strategy prioritization activities; and discuss community action planning. For each of the seven planned meetings, the Topic groups will meet separately; thus, each will develop their own conceptual models and list of prioritized strategies.

In the Delphi county, the community research team will identify which stakeholders to include in the intervention using discussion-based consensus. They will also finalize the contents of the surveys to be used to solicit information from participants via the Delphi method. Delphi participants will attend an introductory meeting facilitated by the local community research team to learn about the Delphi method; review and discuss data about opioids, opioid misuse, local statistics, and services. They will then receive an online survey asking them to identify strategies and a second online survey asking them to prioritize strategies. After each survey, they will receive a summary of the findings by email. The community research team will bring all Delphi participants together again to discuss the results and community action planning. All stakeholders will participate in the surveys and group meetings together, thus developing one set of strategies.

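### Table 4's minimum detectable differences correspond to 144 participants per arm rather than the planned 72, and show no trace of the stated ICC adjustment; power at the printed total-score difference is about 51%, not 80%

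*Protocol article*

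**What the plan says.** The Recruitment section sets the size: "The target is 48 participants per county (144 total"). The Sample size and power analysis section repeats it by arm: "A target number of 48 participants per community will be recruited and randomized to the intervention or control condition (24 per condition"). Over three counties that is 72 intervention and 72 control participants.

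The same section describes the calculation as "setting the alpha error at 0.05 and the beta error at 0.20", and "adjusting for the estimated ICC and the usual population variances based on cited research (Table 4"). It concludes that "the anticipated sample size will have an 80% probability of detecting treatment differences in the primary outcomes" if the true differences are of the size tabulated. Table 4 is labelled with an estimated n of 144. Its primary row (mean, SD, MDD, percent MDD) reads "Mobilization Scale (Total) 1.87 0.37 0.12 (6.5"). The participation row gives 1.70, 0.56, 0.18 (10.9) and the motivation row 1.83, 0.56, 0.18 (10.1). No ICC value, cluster size or baseline correlation is given.

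On delivery, Table 3 shows three groups of 8 in each SEED county and, for Delphi, "24 (1 group, with number of specific stakeholder groups TBD"). The Implementation section says of the SEED groups and the strategies they rank: "For each of the seven planned meetings, the Topic groups will meet separately; thus, each will develop their own conceptual models and list of prioritized". Controls complete two online surveys. The Randomization section allocates individuals, not groups.

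**The concern.** An ICC adjustment for positive clustering makes an MDD larger than the simple two-arm value. Table 4's values are smaller than that value for this trial, so neither the sample size nor the adjustment described in the text can be recognised in them.

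The 80% claim reads as already protected against clustering. If it rests on twice the planned number per arm and on no allowance for clustering, the trial can reliably detect only considerably larger differences than it states. A null result would then be over-read as evidence that effects of about 6.5% on the Mobilization Scale had been ruled out.

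**Working it through.** **Inputs.** Alpha 0.05, beta 0.20, means, SDs and printed MDDs: Sample size and power analysis, Table 4. Arm sizes and delivery groups: Table 3 (72 versus 72; six Topic groups of 8, one Delphi group of 24). Sidedness is not stated; two-sided is assumed. ICC values are not in the document; 0.01 to 0.10 is an assumed range. All results use the normal approximation.

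**Step 1: reproduce Table 4.** z = 1.960 + 0.842 = 2.802.

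MDD = z × SD × √(2/144):
- Total: 2.802 × 0.37 × 0.11785 = 0.1222; /1.87 = 6.53% (printed 0.12, 6.5)
- Participation: 2.802 × 0.56 × 0.11785 = 0.1849; /1.70 = 10.88% (printed 0.18, 10.9)
- Motivation: 0.1849; /1.83 = 10.10% (printed 0.18, 10.1)

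Every printed digit agrees. In the two-arm formula √(1/n + 1/n), the term √(2/144) means n = 144 per arm; it is also what a one-sample formula with n = 72 gives. On this formula, the rounding limits of the percentages leave a variance multiplier of 0.995 to 1.005 across the rows, so there is no visible inflation. The rows share one multiplier, so this is one match with tight rounding, not three independent ones.

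**Step 2: the planned 72 versus 72, no clustering.** MDD = 2.802 × SD × √(2/72):
- Total: 2.802 × 0.37 × 0.16667 = 0.173 (9.2%)
- Participation: 0.261 (15.4%)
- Motivation: 0.261 (14.3%)

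The printed values are too small by √2; on 72 per arm they imply a variance multiplier of about 0.50. A one-sided alpha does not rescue them: it gives 0.153 (8.2%) for the total score.

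**Step 3: power at the printed difference.** Standard error of the total-score contrast = 0.37 × √(2/72) = 0.0617. Power at 0.122 = Φ(0.1222/0.0617 − 1.96) = Φ(0.021) ≈ 51%. At exactly 0.12 it is about 49%.

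**Step 4: clustering by delivery group.** Individuals are randomized within county, so a county-level ICC alone need not inflate the between-arm variance. The clustering that matters is within Topic and Delphi groups, in the intervention arm only.

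Variance of the intervention mean = SD²/72 × [1 + ((48×7 + 24×23)/72) × ICC] = SD²/72 × (1 + 12.33 × ICC).

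With independent controls, the design effect on the contrast is (2 + 12.33 × ICC)/2 = 1 + 6.17 × ICC. Of the 12.33, the Delphi group supplies 24×23/72 = 7.67 (62%). If its correlation is negligible, the coefficient is 48×7/72 = 4.67 and the design effect is 1 + 2.33 × ICC.

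Total-score MDD at 72 per arm:

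| Assumed ICC | All delivery groups: design effect, MDD | Delphi negligible: design effect, MDD |
|---|---|---|
| 0 | 1.00, 0.173 | 1.00, 0.173 |
| 0.01 | 1.06, 0.178 | 1.02, 0.175 |
| 0.05 | 1.31, 0.198 | 1.12, 0.183 |
| 0.10 | 1.62, 0.220 | 1.23, 0.192 |

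With ICC 0.05 in all groups, power at 0.122 is Φ(1.981/√1.308 − 1.96) ≈ 41%.

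**The case against.** The strongest counter-argument is that the outcome is change over three time points, and Table 4 may include a credit for correlation with baseline. On 72 per arm with no clustering, an ANCOVA credit needs 1 − r² = 0.50, so r ≈ 0.71; a change-score credit needs 2(1 − r) = 0.50, so r = 0.75. With a design effect above 1, a higher r would do the same: about 0.79 by ANCOVA at ICC 0.05 in all delivery groups. A genuine ICC inflation could therefore be hidden behind such a credit. This stands as a caveat. It is the less likely explanation because no credit is mentioned and the multiplier would have to fall almost exactly on one half, which is what entering 144 per arm gives directly.

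A second argument is that the only ICC level the article names, in Data analysis, is the community. That is correct, and the delivery-group ICCs used here are assumptions. It limits how far the size of any clustering penalty can be claimed. It does not explain why the printed values lie below the unclustered ones.

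A reader might infer that the absent ICC term is the main reason the 80% is too high, or that the document proves an ICC of zero was used. Neither is supported. A design effect of exactly 1.00 follows only if 144 is entered per arm, and the √2 error costs about 29 percentage points of power before any clustering. By comparison, at a difference set for 80% power without clustering, an ICC of 0.01 in all delivery groups lowers power to 78% and 0.05 to 69%. Nor should the larger clustering figures be taken as established: they give the Delphi group, which shares an introductory meeting, two surveys and a results meeting, the same ICC as Topic groups that meet seven times.

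That a condensed article omits the ICC value is not itself the fault. The fault is that it states an adjustment which its own table does not show.

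**Conclusion.** The point holds in this form: Table 4 does not correspond to the planned 72 per arm, and the claimed ICC adjustment is not visible in any row. The first is the larger error. Without clustering or a baseline credit, the MDDs should be 0.173, 0.261 and 0.261 instead of 0.12, 0.18 and 0.18, and power at the total-score difference behind the printed 6.5% is about 51%.

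Clustering adds to this by an amount the document does not allow one to fix: over assumed ICCs of 0.01 to 0.10, the total-score MDD is 0.178 to 0.220 with all delivery groups correlated, or 0.175 to 0.192 with negligible Delphi correlation. With only seven delivery groups, the normal approximation is somewhat optimistic. The conclusion assumes a two-sided test, the Table 4 SDs, full recruitment and no undisclosed baseline-correlation credit.

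**What to change.** In Sample size and power analysis, recompute Table 4 with 72 per arm and the partially nested variance, SD²/72 × [1 + (1 + 12.33 × ICC)], over a stated ICC range such as 0.01, 0.05 and 0.10. Add a version with little or no correlation in the Delphi group (4.67 in place of 12.33). State the ICC, the level it refers to and any baseline correlation credited. Restate the 80% claim at the recomputed MDDs.

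If no ICC was in fact applied, remove the phrase claiming the adjustment as well as correcting the per-arm n. Removing the phrase alone would leave 0.12, 0.18 and 0.18 and the 80% claim wrong by √2.

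The cost is one table and a few sentences, with less favourable stated MDDs. No change to enrolment or data collection is needed.

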### Interventions

Two counties will use the SEED Method and one county will use a modified Delphi method. We were originally funded to implement the SEED Method in three counties but decided to implement the Delphi method in one county for comparative and logistical reasons.

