### Methods and analysis

The aim of the proposed study is to increase the level of evidence for community-engaged research methods through a randomized controlled trial. The research objectives are to evaluate the effectiveness of the SEED Method and compare it to a modified Delphi method in opioid action planning projects in three rural Virginia communities.

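### The 80% power statement and Table 4 fit only the pooled intervention v control contrast (n = 144), but are not limited to it; the planned SEED v control, Delphi v control and SEED v Delphi contrasts fall short of 80% at the printed differences

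*Protocol article*

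**What the plan says.** All references are to the protocol article.

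- **Sample size and power analysis** gives one power claim, "the anticipated sample size will have an 80% probability of detecting treatment differences in the primary outcomes". It is conditional on true differences being about the minimum detectable differences (MDDs) in Table 4. The settings are "setting the alpha error at 0.05 and the beta error at 0.20". Table 4 is headed "Estimated *n* = 144" and prints, for the Mobilization Scale total, mean 1.87, SD 0.37 and MDD 0.12 (6.5%). Both subscales have SD 0.56 and MDD 0.18. The text says an ICC was allowed for but gives no value.
- **The same section, with Table 3**, sets the allocation: "A target number of 48 participants per community will be recruited and randomized to the intervention or control condition (24 per condition").
- **Interventions** says "Two counties will use the SEED Method and one county will use a modified Delphi method". It adds: "We were originally funded to implement the SEED Method in three counties but decided to implement the Delphi method in one county".
- **Methods and analysis** gives the objectives as "to evaluate the effectiveness of the SEED Method and compare it to a modified Delphi method".
- **Research questions** lists SEED against Delphi first, then intervention against control without separating the two methods.
- **Discussion** says "we will be able to compare the SEED Method to the Delphi Method and compare both of these methods to the control group".

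**The concern.** The article commits to four contrasts: pooled intervention v control, SEED v control, Delphi v control, and SEED v Delphi. It gives one N, one set of MDDs and one power figure. The N of 144 belongs to the pooled contrast. The other three use fewer participants or divide them differently, and the text does not say that the 80% leaves them out.

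The Discussion presents the trial as helping researchers and communities choose between engagement methods, so the method-specific results are the ones readers will look for. A non-significant Delphi result from 24 v 24 would be read against a published 80% power that this contrast does not have at the printed difference, and could be taken as evidence that Delphi has no effect.

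**Working it through.** **Inputs.** Alpha 0.05, taken as two-sided because sidedness is not stated; power 80%; SD 0.37; mean 1.87; printed MDD 0.12 (all from Sample size and power analysis). Allocation is 24 v 24 in each of three counties, two SEED and one Delphi (Table 3). No ICC or dropout is applied because no value is given for either; this favours the plan.

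**Step 1: the plan's own figure.** MDD = (1.960 + 0.842) × SD × √(1/n₁ + 1/n₂).

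- 72 v 72: 2.802 × 0.37 × √(2/72) = 0.173, or 9.2% of 1.87. This is not the printed figure.
- 144 v 144: 2.802 × 0.37 × √(2/144) = 0.122, or 6.5%. This is the printed figure.
- Subscales with 144 per arm: 2.802 × 0.56 × √(2/144) = 0.185, which is 10.9% of 1.70 and 10.1% of 1.83, again as printed.

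Table 4 therefore matches 144 per arm. It also matches 72 v 72 if the variance is halved, for example by a pre-post correlation of 0.75 with change scores or 0.71 with ANCOVA, but no such correlation is stated. Both readings are carried forward.

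**Step 2: contrast sizes from Table 3.** SEED v its own-county controls, 48/48. Delphi v its own-county controls, 24/24. SEED v Delphi, 48/24.

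**Step 3: power and MDD by noncentral t.** The standardised difference is 0.12/0.37 = 0.324 with the printed SD. With halved variance, the SD is 0.37/√2 = 0.262 and power is taken at the unrounded 0.122.

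| Contrast | n₁/n₂ | Power at 0.12, printed SD | Power at 0.122, variance halved | MDD at 80%, printed SD |
|---|---|---|---|---|
| Pooled intervention v control | 72/72 | 49% | 80% | 0.17 |
| SEED v control | 48/48 | 35% | 62% | 0.21 (11.4%) |
| Delphi v control | 24/24 | 20% | 35% | 0.31 (16.3%) |
| SEED v Delphi | 48/24 | 25% | 45% | 0.26 (14.1%) |
| SEED v all controls | 48/72 | 41% | 70% | 0.19 |
| Delphi v all controls | 24/72 | 28% | 50% | 0.25 |

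**Step 4: how much is due to contrast size alone.** At the 72 v 72 MDD of 0.174 with the printed SD, the pooled contrast has 80% power. The three own-county contrasts have 63%, 36% and 46%.

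**Step 5: SEED v Delphi net of controls.** If each method's effect is first taken against its own-county controls, SE = 0.37 × √(1/48 + 1/48 + 1/24 + 1/24) = 0.131, and the MDD is 2.802 × 0.131 = 0.37.

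**The case against.** The strongest reply is that the power statement was only ever about the pooled contrast. Research questions asks about intervention v control without splitting by method, the power section counts intervention and control participants together, and Table 4 prints its N. This is the most natural reading of the 144. A reader might infer that no planned contrast corresponds to the stated N; the documents do not support that. What stands against the reply is that the 80% is claimed for treatment differences generally, while the Discussion promises the method-specific comparisons as something the design delivers.

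Other replies limit the point:

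- The 80% is conditional on the MDD. The method-specific contrasts lack 80% power at the Table 4 differences, not at every effect size.
- It would be tempting to put the whole shortfall at 0.12 down to contrast size. Much of it belongs to the separate problem in Table 4, since 72 v 72 itself has 49% there.
- The exact MDDs depend on choices the article leaves open. The outcome is a change analysed longitudinally with covariates, so a pre-post correlation could reduce the variance; with it halved, the normal-approximation MDDs are 0.150, 0.212 and 0.183. That Delphi v control can detect only a very large difference is therefore not established.
- Methods and analysis does not itself name Delphi v control; the Discussion does.
- The change from three SEED counties to two might suggest that Table 4 was carried over from the earlier design. The article does not say so, and the point does not need it.

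The full protocol or analysis plan may hold further power figures. But the article chose to publish a power claim alongside these comparisons, and its general remark about small sample size does not restrict that claim.

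**Conclusion.** The point holds in limited form. The single 80% statement and Table 4 fit only the pooled 72 v 72 contrast by their N, and the article does not limit the claim to that contrast. SEED v control, Delphi v control and SEED v Delphi have about 35%, 20% and 25% power at 0.12 with the printed SD. On the reading most favourable to Table 4 they have about 62%, 35% and 45%. Pooling controls across counties raises the first two to 41% and 28%, or about 70% and 50% on the favourable reading. No variant reaches 80%.

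These figures assume two-sided alpha 0.05, full recruitment and no clustering; a positive ICC or dropout would lower them. It should not be inferred that the pooled contrast has its stated power: with the printed SD its MDD is about 0.17, not 0.12, unless an unstated variance reduction was used. This is a reporting fault that should be corrected. It does not invalidate the design.

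**What to change.** In Sample size and power analysis:

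1. Limit the 80% statement to pooled intervention v control, at its corrected MDD (about 0.17 with the printed SD and no ICC), and state the n per arm, the ICC and any pre-post correlation used.
2. Add to Table 4 an MDD for each of SEED v control, Delphi v control and SEED v Delphi, computed with the authors' own ICC, correlation and choice of controls. As illustration only, the printed SD with no ICC gives about 0.21, 0.31 and 0.26, or about 0.37 for SEED v Delphi net of own-county controls.
3. Alternatively to item 2, label these three contrasts exploratory and report them as estimates with confidence intervals.

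The cost is a revised table and a few sentences. The stated MDDs become less favourable; no extra participants are needed.
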